## Abstract

**Background:**

The development of optimal strategies to treat impaired mobility related to ageing and chronic disease requires better ways to detect and measure it. Digital health technology, including body worn sensors, has the potential to directly and accurately capture real-world mobility. Mobilise-D consists of 34 partners from 13 countries who are working together to jointly develop and implement a digital mobility assessment solution to demonstrate that real-world digital mobility outcomes have the potential to provide a better, safer, and quicker way to assess, monitor, and predict the efficacy of new interventions on impaired mobility. The overarching objective of the study is to establish the clinical validity of digital outcomes in patient populations impacted by mobility challenges, and to support engagement with regulatory and health technology agencies towards acceptance of digital mobility assessment in regulatory and health technology assessment decisions.

**Methods/design:**

The Mobilise-D clinical validation study is a longitudinal observational cohort study that will recruit 2400 participants from four clinical cohorts. The populations of the Innovative Medicine Initiative-Joint Undertaking represent neurodegenerative conditions (Parkinson’s Disease), respiratory disease (Chronic Obstructive Pulmonary Disease), neuro-inflammatory disorder (Multiple Sclerosis), fall-related injuries, osteoporosis, sarcopenia, and frailty (Proximal Femoral Fracture). In total, 17 clinical sites in ten countries will recruit participants who will be evaluated every six months over a period of two years. A wide range of core and cohort specific outcome measures will be collected, spanning patient-reported, observer-reported, and clinician-reported outcomes as well as performance-based outcomes (physical measures and cognitive/mental measures). Daily-living mobility and physical capacity will be assessed directly using a wearable device. These four clinical cohorts were chosen to obtain generalizable clinical findings, including diverse clinical, cultural, geographical, and age representation. The disease cohorts include a broad and heterogeneous range of subject characteristics with varying chronic care needs, and represent different trajectories of mobility disability.

**Discussion:**

The results of Mobilise-D will provide longitudinal data on the use of digital mobility outcomes to identify, stratify, and monitor disability. This will support the development of widespread, cost-effective access to optimal clinical mobility management through personalised healthcare. Further, Mobilise-D will provide evidence-based, direct measures which can be endorsed by regulatory agencies and health technology assessment bodies to quantify the impact of disease-modifying interventions on mobility.

**Trial registration:**

ISRCTN12051706.

## Introduction

A key challenge for delivering healthcare in ageing societies is the optimal evaluation of mobility, which can be broadly defined as the ability and performance of a person to move about in their environment [1]. Central aspects of mobility according to the World Health Organization (WHO) are changing one’s body position or location; or transferring from one place to another; carrying, moving or manipulating objects; or walking, running or climbing [2].

Walking is the most common and functionally relevant aspect of mobility that is affected by age-associated processes and multiple chronic diseases. Walking is a complex activity that requires interactions between the cardiovascular, pulmonary, and musculoskeletal systems as well as widespread brain networks for effective performance [3]. Deteriorations in these systems are reflected in walking performance. As such, walking speed is increasingly denominated as the “6^th^ vital sign of health” [4] and represents an appropriate mobility measure for multiple populations. This is mirrored by strong evidence that mobility outcomes, such as walking speed and physical activity predict morbidity, mortality, falls, cognitive impairment, and disability [5–10]. It is, therefore, not surprising that people living with chronic conditions often rate physical mobility–and specifically walking ability–as one of the most important clinical outcome measures [11–15].

Currently, clinical research and practice mainly rely on patient-reported outcomes (self-reported/perceived walking capacity/ability), objective clinical assessments of walking capacity, and subjective clinical assessments (clinician-led evaluation of walking capacity). All assessments are subject to recall and response bias, are often burdensome in their execution (for both patients and assessors), have ceiling or floor effects, Hawthorne effects, and/or other limitations [16–18]. Fluctuations due to medication and disease exacerbation further reduce reliability and validity due to the intermittent nature of assessment. Moreover, these assessments are regularly conducted in lab-based or clinical environment which do not necessarily reflect the complex environmental determinants of functional mobility in daily life, which severely hampers their ecological validity [16, 19–21]. Variations in the environment for these measurements can include supervised and controlled settings to measure capacity vs. non-supervised and uncontrolled environments [2]. Despite the identified need for quantitative mobility assessment under multiple conditions, inconsistent testing procedures and wide variations in baseline "norms" have prevented the establishment of a widely adopted consensus on walking and mobility outcomes. Consequently, there is no harmonised approach to the measurement and understanding of impaired, real-life mobility.

### Rationale

There is a clinical need for mobility assessment to reflect real-world performance. In the last decade, advances in sensor technology, largely driven by the consumer market, have led to the advancement of wearable sensors that are able to record continuously for longer periods of time and include multi-sensing capabilities. Measurements can be obtained remotely [22–24], opening up opportunities to extend the scope of mobility measurement to continuously capture discrete and clinically relevant mobility characteristics. It is now feasible to conduct objective, digital mobility assessment during real-world walking, defined as unsupervised, unscripted walking behaviour which occurs in non-simulated everyday situations [16]. These walking-related digital mobility outcomes (DMOs) such as volume, pace, rhythm, variability, and symmetry are increasingly used to quantify as well as qualify gait in multiple medical conditions.

Emerging evidence suggesting that DMOs are sensitive as well as ecologically valid markers of health status has evoked calls for validation and qualification by seeking regulatory approval for DMOs as clinical endpoint measures [25–30]. However, studies are needed to establish their construct validity, predictive validity, responsiveness and clinical meaningfulness [31–33]. The most recent systematic evidence [34, 35] supports the need for clinical validation of DMOs within Mobilise-D.

A multi-centric observational study [36] is being conducted as part of Mobilise-D to establish the technical validity and patient acceptability of the approach used to quantify digital mobility in the real-world. This technical validation study (TVS) allowed the definition of a set of procedures for the metrological verification of an inertial sensor-based device and for the experimental validation of the algorithms used to calculate the DMOs. The experimental validation included laboratory and real-world assessment in participants from five disease groups (chronic obstructive pulmonary disease (COPD), Parkinson’s disease (PD), multiple sclerosis (MS), proximal femoral fracture (PFF), and congestive heart failure). The DMOs extracted from the device were validated against those from different reference systems, chosen according to the contexts of observation. Questionnaires and interviews were used to evaluate the users’ perspective on the deployed technology and the relevance of the mobility assessment.

### Mobility constructs

Within Mobilise-D, there are three distinct mobility constructs being measured and assessed: what a person i) can do, ii) thinks they do, and iii) actually do in real life [29, 37]. *Mobility capacity* represents the ability of a patient to move and is provided by supervised clinical tests such as the six-minutes walking test (6-MWT), supervised gait speed or clinician-assigned scores based on clinical tests. This is what a person can do. *Mobility perception* represents the patient’s subjective perception of their own mobility, and is provided through patient reported outcomes (PRO) or clinician-assigned scores based on the patient’s answers to standardised questionnaires. It captures what the patient or clinician thinks the patient does. *Mobility performance* represents the duration, quality, and intensity of the participant’s mobility as observed in unsupervised real-world settings, and during observational periods of time that are sufficiently long enough in duration to be considered representatives of the daily life. This is what a person actually does in their real life. Disparities between parameters has been shown depending on which construct was being assessed [38]. There are currently no biomarkers accepted by regulators or accepted across diseases to quantify mobility performance [31–33]. At present, in the regulatory evaluation of new or existing drugs targeting chronic diseases, mobility is frequently estimated in short and cohort specific lab-based assessments, rather than day-to-day performance over time [39].

### Aim and objectives

Mobilise-D Clinical Validation Study (CVS) aims to deliver and validate a new methodology for real-world digital mobility assessment to monitor and predict global and disease-specific clinical outcomes in a variety of disease states: PD, COPD, MS, and PFF. This will be used to obtain regulatory and health stakeholder approval for digital mobility assessment.

Within the clinical validation study, the objectives include:

Assessing the construct validity of DMOs against established clinically relevant constructs;Defining predictive capacity of DMOs against general and disease-specific, clinically relevant constructs;Assessing the ability of DMOs to detect change over time in clinically relevant constructs;Estimating the Minimal Important Difference (MID) of DMOs to measure change in disease state (worsened or improved)Describing real-world walking behaviour with DMOs in patients with PD, MS, COPD and following PFF.

## Materials and methods

The SPIRIT reporting guidelines have been followed within this manuscript [40], see Fig 1. This protocol represents version 1.5; March 2022.

**Fig 1 pone.0269615.g001:**
[figure not shown]
List of assessments and outcomes collected during screening, baseline assessment and every six months. T1, Screening/Baseline; T2, 6 month assessment; T3, 12 month assessment; T4, 18 month assessment; T5, 24 month assessment; *, indicates key (primary) cohort specific outcome measure; SPPB, short physical performance battery–PFF key primary cohort specific outcome measure; † falls and fracture data are collected retrospectively, 12 month retrospective at T1 and 6 month retrospective at T2-T5; β, pre-fracture status is measured at T1, current status is measured at T3 and T5; α, only applicable to acute patients; Outcome type, type of outcome measure in accordance with FDA terminology; COA, clinical outcome measure–describes or reflects how a patient feels, functions, or survives; PRO, Patient-reported outcome; ObsRO–Observer-reported outcome; ClinRO, Clinician-reported outcome; PerfO, Performance-based outcome; PerfO-P, Performance-based outcome physical measure; PerfO-C, Performance-based outcome cognitive/mental measure; Construct, validation construct assessed; PC, predictive capacity; CV, construct validity; DC, detect change over 24 months; MID, Minimum Important Difference; MC, medical chart.

### Study design and setting

Mobilise-D CVS is a longitudinal, observational cohort study, funded by the EU Innovative Medicine Initiative (IMI), which will include 2400 participants from four disease cohorts recruiting from 17 clinical sites across ten countries (Belgium, France, Germany, Greece, Israel, Italy, Norway, Spain, Switzerland, United Kingdom).

### Study procedure and study flow

#### Recruitment and screening

Participants are identified through research registries, out-patient and in-patient services. Potentially eligible and interested participants are invited to a screening appointment during which informed consent is obtained and eligibility is confirmed. (Informed consent forms available within the appendices). Rates of eligibility are monitored. Details of the recruitment process are shown in Fig 2. Each participant will be followed-up every 6 months for a total of 24 months (Fig 3); screening and baseline assessment (T1) must be completed at the respective clinical site; T2 to T5 should also be completed at site, but can be completed at the participants’ home under exceptional circumstances to minimise drop-out and loss to follow-up.

**Fig 2 pone.0269615.g002:**
[figure not shown]
Flow chart to illustrate full recruitment process.

**Fig 3 pone.0269615.g003:**
[figure not shown]
Study flow.

Participants’ flow through the study is documented and presented in a Consolidated Standards of Reporting Trials flow diagram [41]. Reasons for dropout are recorded and data collected up to the time of withdrawal will be included in analyses unless the participant withdraws their consent.

#### Participants

The four disease cohorts studied within Mobilise-D CVS are Parkinson’s Disease (PD), Multiple Sclerosis (MS), Chronic Obstructive Pulmonary Disease (COPD) and Proximal Femur Fracture (PFF). Participants have to meet the core eligibility criteria as well as their respective cohort eligibility criteria. The full inclusion and exclusion criteria are listed in Table 1.

**Table 1 pone.0269615.t001:** Inclusion and exclusion criteria.

Cohort	Inclusion Criteria	Exclusion Criteria
**All**	• Able to walk 4 meters independently with or without walking aids • Anticipated availability for repeated study visits over 24 months • Ability to consent and comply with any study specific procedures. • Willingness to wear a wearable sensor for mobility monitoring • Able to read and write in first language in the respective country	• Occurrence of any of the following within 3 months prior to informed consent: myocardial infarction, hospitalization for unstable angina, stroke, coronary artery bypass graft (CABG), percutaneous coronary intervention (PCI), implantation of a cardiac resynchronization therapy device (CRTD), active treatment for cancer or other malignant disease, uncontrolled congestive heart disease (NYHA class >3), acute psychosis or major psychiatric disorders or continued substance abuse
**PD**	• Aged 18 or over • Patients with the clinical diagnosis of PD according to the recent criteria of the Movement Disorder Society^2^ • Hoehn & Yahr stage I-III	• History consistent with Dementia with Lewy Bodies (DLB), atypical parkinsonian syndromes (including multiple system atrophy or progressive supranuclear palsy, diagnosed according to accepted criteria) • Repeated strokes or stepwise progression of symptoms, leading to a diagnosis of ‘vascular parkinsonism’ • Drug-induced Parkinsonism
**MS**	• Aged 18 or over • A diagnosis of MS based on the revised McDonald’s criteria • EDSS score of 3.0–6.5 • Clinical evidence of disability worsening over the previous two years	• Clinical relapse within 30 days prior to screening and baseline.
**COPD**	• Aged 18 or over • Diagnosis of COPD (post-bronchodilator forced expiratory volume in the first second (FEV_1_) to forced vital capacity (FVC) ratio <0.70 • Clinical stability, defined as at least 4 weeks after the onset of the last exacerbation • Current or ex-smokers with a smoking history equivalent to at least 10 pack years (1 pack year = 20 cigarettes smoked per day for 1 year)	• Having undergone major lung surgery (e.g. lung transplant) • Current diagnosis of lung cancer • Primary respiratory diseases other than COPD • Substantial limitations in mobility due to factors other than COPD • Lung volume reduction within 6 months before inclusion
**PFF**	• Aged 45 or over • Surgical treatment (fixation or arthroplasty) for a low-energy fracture of the proximal femur (ICD-10 diagnosis S72.0, S72.1, S72.2) as diagnosed on X-rays of the hip and pelvis. Between 3 days and 52 weeks post-surgery	• Not able to walk before treatment of hip fracture

The disease cohorts have been chosen because they represent different classes of mobility problems relating to low physical activity, different gait disturbances, and frailty, each affecting large groups of European citizens over substantial periods of time. The disease cohorts include a broad and heterogeneous range of subject characteristics with varying chronic care needs, and represent different trajectories of disability.

### Cohort descriptions

In the PD cohort, participants with mild to moderate disease state will be included (Hoehn & Yahr stage 1–3), which is of interest due to: 1) PD being a progressive disease, so the evaluation of a mobility endpoint over the course of two years can provide insight into disease trajectories; 2) PD being a heterogeneous disease, so the assessment of mobility endpoints in this disease can give relevant insight into the sensitivity to change of this endpoint across a broad range of mobility patterns; 3) improving our understanding of the association of mobility disability with falls and the influence of PD-specific symptoms on mobility in particular; and 4) PD being associated with characteristic gait disorders that can validate the Mobilise-D gait algorithm also for "challenging" gait deficits.

In the COPD cohort, patients with different COPD severity will be included, from those with mild disease and little burden of disease to those with very severe disease and significant burden and mobility impact. This represents the typical sample of patients recruited in clinical trials investigating pharmacologic and non-pharmacologic interventions. Exacerbations are events that punctuate the disease progression in COPD and their occurrence marks moments of acute deterioration and are often followed by only partial recovery. In the COPD cohort particular attention will be given to these events and how they interact with mobility in particular mobility decline. Mobilise-D will allow the study of mobility worsening over time in relation to other relevant clinical outcomes. In addition, the collection of treatment data will allow identification of patients undergoing pulmonary rehabilitation programs which offers insight in mobility improvement trajectories.

The MS population will be based on the revised McDonald’s criteria, with mild to moderate disability., Patients will be recruited covering a wide spectrum of overall disability and varying severity of walking impairment, with Expanded Disability Status Scale from 3—fully ambulatory but with mild to moderate disability in other functional systems—to 6.5 –indicating reduced walking distance and requiring walking aids to walk 20 meters without resting. They will also have had disability progression over the previous two years, to enrich the sample with patients who are likely to progress over the next two years. Patients with a recent relapse (30 days before screening) will be excluded in order to have a reliable mobility measure not impacted by the recovery from a relapse.

The PFF cohort will be recruited either during the acute postoperative or subacute phase (max. 52 weeks) following sustaining a hip fracture. All PFF participants are community dwelling at point of enrolment; care home residents will not be included due to their increased burden of comorbidities likely to bias mobility results. Enrolling acute PFF patients allows monitoring of mobility during the recovery phase over the first 12 months providing unprecedented analysis of mobility trajectories over a long period of time in a disease cohort where mobility impairment is the direct consequence of a major trauma. Enrolling subacute PFF participants will allow a longer follow-up of mobility to focus on functional decline in a population with a high prevalence of frailty and sarcopenia. The aim is to study a mixed population of older community-dwelling adults to capture those who received for informal and formal care as well as participants who were independent prior to sustaining a hip fracture.

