#### Analysis plan

The statistical analysis will follow a pre-specified step-wise procedure. We will elaborate a Statistical Analysis Plan including the definition of analysis sets, details on data edition (including derivation of new variables), handling of missing data and statistical analysis (including prioritisation of outcomes).

Descriptive analysis of main characteristics of patients, including detailed description of COAs and DMOs, will be done by number and percentage for categorical variables, mean and standard deviation for continuous variables with normal distribution, and median and percentiles 25th-75th for continuous variables with non-normal distribution.

We will test construct validity (convergent and known-groups). For convergent validity, we will test the correlation (Pearson or Spearman, depending on variables distribution) between DMOs and related constructs. A table of expected correlations for each DMO-construct combination will be built based on existing literature. For known-group validity, we will use one-way ANOVA test and pairwise comparisons of means between groups a priori expected to have differences in DMOs values. To test predictive capacity of DMOs against the disease-specific and global outcomes we will estimate the association between baseline DMO levels and each outcome using multivariable regression models (specific models depending on outcome distribution) adjusting for confounders. Non-linear associations will be tested using generalised additive models and appropriate transformation of variables will be done consequently. Secondary analyses will include use of DMO changes over time as predictors, and adjusting for baseline levels as sensitivity analysis. The ability of each DMOs to predict disease-specific and global outcomes will be compared to that of traditional predictors and predictive scores.

To quantify the ability to detect change of DMOs, we will calculate the change (between baseline and different follow-up periods) and the standardised response mean (SRM) in (1) groups defined by the self-reported change in mobility, (2) groups defined according to having had a clinically relevant event (e.g., an exacerbation in COPD, a fall in Parkinson) during follow-up, and (3) groups defined according to clinically relevant changes in anchors.

We will establish the MID by triangulation using anchor- and distribution-based estimates.

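### In the hip-fracture (PFF) cohort, change measured from T1 mixes remaining recovery with later decline, to a degree set by weeks since surgery at entry

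*Protocol article*

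**What the plan says.** Table 1 admits PFF participants "Between 3 days and 52 weeks post-surgery". Cohort descriptions says that they are recruited "either during the acute postoperative or subacute phase (max. 52 weeks) following sustaining a hip fracture", without giving a boundary between acute and subacute. It then gives each group a purpose. For the acute group: "Enrolling acute PFF patients allows monitoring of mobility during the recovery phase over the first 12 months". For the subacute group: "Enrolling subacute PFF participants will allow a longer follow-up of mobility to focus on functional decline".

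Follow-up is counted from enrolment, not from surgery: "Each participant will be followed-up every 6 months for a total of 24 months", with the visits labelled in the Fig 1 legend as "T1, Screening/Baseline; T2, 6 month assessment; T3, 12 month assessment" and so on to T5 at 24 months.

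The Analysis plan section has one paragraph on ability to detect change, written for all four cohorts: "we will calculate the change (between baseline and different follow-up periods) and the standardised response mean (SRM"), in groups defined by self-reported change in mobility, by a clinically relevant event during follow-up, or by clinically relevant change in anchors. The stated objectives include a minimal important difference (MID) for both worsening and improvement. A separate statistical analysis plan is announced and is not shown.

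**The concern.** In PD, MS and COPD, participants enter in a more or less stable state, so a change from T1 has a similar meaning for all of them. The protocol protects that meaning: it excludes MS patients with a recent relapse so that recovery does not affect the mobility measure, and it requires COPD patients to be at least 4 weeks past the onset of an exacerbation. PFF participants are, deliberately and legitimately, recruited while recovering, yet the same baseline reference is stated for them.

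A PFF change score from T1 then has two components that run in opposite directions, and their balance depends on when the participant happened to enrol. Pooled over entry times, the two partly cancel. In an event-defined group, someone who falls while still recovering can show a positive change in a digital mobility outcome (DMO) because recovery outweighs the effect of the fall. The SRM would then misstate responsiveness to worsening. An estimate of functional decline, the stated reason for enrolling subacute participants, would be biased towards no decline.

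**Working it through.** **Inputs from the protocol.** Entry week w runs from 3 days (0.43 weeks) to 52 weeks after surgery (Table 1). Visits T1 to T5 are 6 months apart (Recruitment and screening). The recovery phase is the first 12 months (Cohort descriptions). The reference for change is baseline (Analysis plan).

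**Assumptions.** 12 months is 52 weeks and 6 months is 26 weeks. Recovery is counted from surgery. Visits occur at their nominal times.

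**Step 1: where the visits fall.** Weeks since surgery at visit k = w + 26(k - 1). T1 is at or before week 52 for everyone. T2 is at week w + 26, so it reaches week 52 only for entry from week 26. T3 is at week w + 52, so it is past week 52 for everyone.

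**Step 2: share of each change interval inside the recovery phase.** Share = min(52 - w, L)/L, where L is 26 weeks for T1-T2, 52 for T1-T3 and 104 for T1-T5.

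| Entry week | T1-T2 | T1-T3 | T1-T5 |
|---|---|---|---|
| 0.43 (day 3) | 100% | 99% | 50% |
| 13 | 100% | 39/52 = 75% | 39/104 = 38% |
| 26 | 26/26 = 100% | 26/52 = 50% | 26/104 = 25% |
| 39 | 13/26 = 50% | 13/52 = 25% | 13/104 = 12.5% |
| 52 | 0% | 0% | 0% |

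**Step 3: average over subacute entrants.** The protocol gives no acute/subacute cut, so a range is needed. With entry assumed uniform from week 6, 13 or 26 up to week 52, the mean share is 72%, 67% or 50% for T1-T2 and 44%, 38% or 25% for T1-T3. For example, from week 13: (13/39) x 1 + (26/39) x 0.5 = 67%.

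**Step 4: illustration of size.** The protocol gives neither the amount of recovery nor the rate of decline, so the curve is assumed: s(t) = g(1 - exp(-t/13)) - 0.03t/52 m/s, with t in weeks since surgery. Recovery g is 0.25 or 0.15 m/s, its time constant is 13 weeks, and decline is 0.03 m/s per year. The T1-T5 change is g exp(-w/13)(1 - exp(-8)) - 0.06.

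| Entry week | T1-T5, g = 0.25 | T1-T5, g = 0.15 |
|---|---|---|
| 0.43 | 0.242 - 0.06 = +0.18 | 0.145 - 0.06 = +0.085 |
| 13 | 0.092 - 0.06 = +0.03 | 0.055 - 0.06 = -0.005 |
| 26 | 0.034 - 0.06 = -0.03 | 0.020 - 0.06 = -0.04 |
| 52 | 0.005 - 0.06 = -0.055 | 0.003 - 0.06 = -0.057 |

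The same underlying decline gives different values, and with g = 0.25 different signs even among participants entering at week 13 or later. Between entry at weeks 13 and 52 the T1-T5 change differs by 0.09 m/s (g = 0.25) or 0.05 m/s (g = 0.15). By comparison, T3-T5 with g = 0.25 is between -0.026 and -0.030 m/s for every entry week, close to the assumed decline of 0.03.

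**Step 5: event groups.** With g = 0.25 and entry at week 13, the T1-T2 change without any event is 0.25 x exp(-1) x (1 - exp(-2)) - 0.015 = 0.080 - 0.015 = +0.06 m/s. An event that costs less than this leaves a positive change.

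**The case against.** The case against is substantial, and part of it stands.

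- *No text says that PFF decline is to be studied only as change from T1.* Correct. The sentence on decline explains why subacute participants are enrolled and names no analysis. The link runs through the general paragraph on change, which is the only change analysis described.
- *A condensed article may leave time since surgery to the analysis plan.* True of covariates and strata, and their absence is not the point here. But the article does state a reference, baseline, for all cohorts, and for PFF that reference gives a confounded result.
- *The grouping already separates the directions.* Largely true for the self-report and anchor groups, and improvement is wanted signal for an MID in both directions. It is not true for event-defined groups or pooled change. The article's own event examples are a COPD exacerbation and a fall in Parkinson's disease, so a PFF event group is an application of the rule, not a quoted case.
- *Recovery is front-loaded, so time shares overstate it.* Fair. On the assumed curve, 37% of recovery remains at week 13 and 14% at week 26, and with g = 0.25 the T1-T2 change is already about zero for entry near week 35 and negative after that.
- *The 12-month recovery phase is stated for acute patients.* Yes. Applying it to subacute patients is a reasonable reading, since both are timed from the same injury, but it is not explicit.

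A reader might infer that early change in every subacute participant is recovery. The 100% to 0% range by entry week rules that out. A reader might also infer that decline cannot be estimated from this study. It can: T3, T4 and T5 lie beyond 12 months for everyone.

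**Conclusion.** The point holds as a poor choice of reference for one cohort. By the protocol's own times, every PFF baseline falls within the recovery phase or at its end, so change and SRM from T1 confound remaining recovery with later decline, by an amount that depends on weeks since surgery at T1. The calendar shares for T1-T2 (100% for entry up to week 26, 50% at week 39, 0% at week 52) need only the convention that recovery is counted in weeks from surgery. The averages also need an assumed entry distribution and subacute start. The m/s figures are an illustration on an assumed curve; the largest of them belong to day-3 entrants, whom the protocol assigns to monitoring of recovery.

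The consequence is limited to pooled and event-defined change and SRM, and to any estimate of functional decline, in PFF. The documents do not support the stronger reading that the protocol contradicts itself or that its design cannot show decline. The matter should be settled before the change analyses are run, and the analysis plan that is not shown may already do so.

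**What to change.** In the analysis plan, for the PFF cohort:

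1. Report T1-based change and SRM stratified by, or adjusted for, weeks since surgery at T1.
2. Estimate functional decline and responsiveness to worsening events from the first follow-up visit at least 52 weeks after surgery through T5. At nominal visit times this is T2 for entry from week 26 and T3 for earlier entry. Because the interval then differs (78 weeks from T2, 52 weeks from T3), express the result as change per unit time or use a mixed model on time since surgery.
3. Add T3-T5 change as a sensitivity analysis on an interval common to all participants. It should not be the only analysis, since it discards usable follow-up after the recovery phase for later entrants.

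Surgery itself cannot serve as the baseline of a change score, because no sensor recording exists before enrolment. Time since surgery enters as the time axis or as a covariate.

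Cost: wording in the analysis plan only. The visits are already scheduled, and time since surgery is already needed to confirm eligibility. The decline interval falls from 24 months to about 18 months for entry from week 26 and about 12 months for earlier entry. The analysis is also restricted to participants still in follow-up at the reference visit, so losses before that visit should be reported and considered in the interpretation.
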